### Intervention

The Anatomic Graduated Component (AGC; Biomet, Inc, Warsaw, IN, USA) is implanted, either the posterior cruciate retaining or the high post posterior stabilized design.

The AGC has been succesfully used in our hospital for over 20 years. We specifically choose this implant since we have very good experiences with it, with a high survival rate. Wordlwide it has been implanted since 1983 with 95%-98% survivorship at 15 years. Several AGC studies have demonstrated these results [6-8].

The AGC consists of a one-piece molded polyethylene tibial component with a durable cobalt chrome femoral component. Regarding the differences between the AGC designs, the posterior cruciate retaining (PCR) design has a posterior cut-out for the posterior cruciate ligament and relatively flat topography. This allows for posterior roll-back of the femur when the knee is flexed and the posterior cruciate ligament is tensioned.

In the posterior stabilized (PS) design the stabilization is achieved by a "cam and post" mechanism added to the prosthesis components. This mechanism replaces the function of the posterior criciate ligament. The femoral component has a transverse cam added to the backside of the prosthesis. The tibial polyethylene plate has a central polyethylene post placed on the middle of the plate. In the assembled total knee, the cylindrical cam comes against the post when the total knee bends. The postthen forces the cam backwards preventing the forward glide of the femoral component. In this way the posterior stabilized total knee replaces the function of the posterior cruciate ligament.

PCR and PS designs from other implants are based on the same biomechanical principles as described above, although there might be some slight differences in design, surgical technique and materials used among different manufacturers. One main advantage of our study, and in which our study differs from others, is that we compare one AGC design with another design of the same implant, which minimizes the variables that differ between the two groups of patients, especially with respect to surgical technique and materials used.

The surgical procedure consists of a midline approach. After the midline skin incision has been made over the knee joint, the capsule of the joint is exposed. By incising the joint capsule, the anteromedial arthrotomy is performed. The capsule is incised anteriorly, just superior to the patella, curving medially from the patella and back down anteriorly, just medial from the patellar ligament.

Antibiotic prophylaxis with a first-generation cephalosporin will be given preoperatively and during the first twenty-four hours intravenously All patients will be treated with the same, standardized protocol postoperatively, in terms of analgesia and mobilization. Subcutaneous low molecular weight heparin is given for 6 weeks postoperatively as prophylaxis against thrombosis. At day one after surgery, physiotherapy is started and patients are mobilized with the aid of two crutches. When patients are able to walk stairs and make transfers to bed and toilet, and when the knee flexes at least 90 degrees, they are discharged from the hospital. Physiotherapy will be continued in the home situation for another 6 weeks.

### Measurements

Measurements will take place preoperatively and 6 weeks, 3 months, 6 months and 1 year postoperatively. In this study the primary outcome parameter is the patient's perceived outcome which will be determined with the Western Ontario and McMaster Universities Osteoarthritis Index (WOMAC). The WOMAC is the most frequently used and recommended questionnaire to determine outcome after TKA [9,10]. The Dutch version has proven to be reliable and valid [11].

Secondary outcome parameters. Physician reported functional status, including range of motion, will be measured with the validated Knee Society Clinical Rating System (KSS) [12]. The 36-item Short Form Health Survey (SF-36) Dutch language version will be used to assess the health related quality of life [13]. Moreover, surgical approach, surgical time and intra-operative blood loss will be recorded and perioperative complications will be registered. The study will be double blinded: the KSS will be completed by a blinded independent observer and the patient will not be informed about which design is used during the length of the study.

### Sample Size

Sample size calculation is based on the primary outcome measure (WOMAC). A difference between the two groups of 15% is considered clinically relevant. With a standard deviation of 19.0 points, α = 0.05 and power of 80%, 55 patients are needed in each group. With an estimated drop-out of 10% in total 120 patients are needed, 60 patients in each group.

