### Statistical analysis

Descriptive statistics (means and standard deviations) will be used to describe the patient characteristics and outcome variables at the 5 measurement points.

A GLM repeated measures analysis will be used to determine whether there is a difference on the primary and secondary outcome variables between the two groups over time. A p-value of < 0.05 is considered significant.

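### The sample-size figures do not close: 60 per group less 10% drop-out leaves 54, not 55, and 55 cannot be reproduced from a 15% difference without a base

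*Protocol article*

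**What the plan says.** The whole calculation stands in one paragraph of the protocol article (Methods, Sample Size). It is based on the WOMAC, the primary outcome. The target and the variability are given together: "A difference between the two groups of 15% is considered clinically relevant. With a standard deviation of 19.0 points". The error rates follow as "α = 0.05 and power of 80" per cent, and the result is "55 patients are needed in each group. With an estimated drop-out of 10% in total 120 patients are needed, 60 patients in each group".

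The Statistical analysis section adds only "A p-value of < 0.05 is considered significant". Neither section says whether the test is one- or two-sided. Nowhere does the article give a reference WOMAC mean, the score (total or subscale) or range used for the calculation, or the target difference in points.

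**The concern.** A comparison of two means needs the difference and the SD in the same unit. Here one is a percentage and the other is in points, and the figure that would convert one to the other is not printed. The 80% power is therefore tied to an undisclosed base. The same sentence defines what counts as clinically relevant, so the doubt carries over to the reading of the primary result, above all a null one.

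Separately, the enrolment figure is meant to leave 55 evaluable patients per group after the expected losses. On the paragraph's own numbers it does not.

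**Working it through.** **Inputs from the Sample Size section:** SD 19.0 points; α 0.05; power 80%; 55 per group evaluable; 10% drop-out; 60 per group enrolled, 120 in total; difference 15%, base not stated. **Assumed:** a simple two-group comparison of means with equal groups; two-sided unless marked.

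**1. Drop-out**

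- Patients left: 60 × (1 − 0.10) = 54 per group, against 55 needed.
- Enrolment that would leave 55: 55 / 0.90 = 61.1, so 62 per group (124 in total).
- Drop-out that 60 per group does cover: 1 − 55/60 = 8.3%.
- Power with 54 per group, for the difference that 55 per group detects with 80% power: about 79.3%.

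**2. Trying to reproduce 55**

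Formula: n per group = 2 × (SD/Δ)² × (z for α + z for power)². Two-sided, (1.960 + 0.842)² ≈ 7.849.

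- 15% read as 15 points: 2 × (19/15)² × 7.849 = 25.2, so 26 per group (the t-test solution is 26.2). With 55 per group the power would be about 98.5%.
- 15% read as 0.15 SD (2.85 points): 698 per group.

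Neither reading gives 55.

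**3. Solving back from 55**

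Δ = SD × √(2/55) × (z for α + z for power).

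- Two-sided: 19 × √(2/55) × (1.960 + 0.842) = 10.15 points (10.24 by t-test), so about 10.2. As 15% of a base: 10.15/0.15 = 67.7 (68.3 by t-test), so a base near 68.
- One-sided: 19 × √(2/55) × (1.645 + 0.842) = 9.01 points; 9.01/0.15 = 60.1, so a base of about 60.
- Forward check: 15% of 68 = 10.2 points, and 2 × (19/10.2)² × 7.849 = 54.5, so 55.

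The stated 55 is thus attainable, but only from a base that the article does not give.

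**4. How much the base matters (two-sided; the bases are assumed, for illustration)**

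| Assumed base | 15% of it, points | n per group for 80% power |
|---|---|---|
| 60 | 9.0 | 70 |
| 65 | 9.75 | 60 |
| 70 | 10.5 | 52 |
| 75 | 11.25 | 45 |
| 80 | 12.0 | 40 |

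Holding 55 per group fixed, power is about 54% for a base of 50 (7.5 points), 70% for 60, 80% for 68 and 91% for 80.

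**The case against.** A relative difference beside an SD in points is an ordinary way to write a sample size: the percentage is applied to a reference mean. That mean and its source may well stand in the full protocol, which a journal article condenses. A base near 68 reproduces 55 exactly. All of this stands, so the missing base shows an incomplete statement and not an arithmetical error in the 55.

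A reader might go further and infer that the trial targets 15 points, needs only 26 per group and is enrolling about twice what it needs. The article does not support that. It says 15%, never 15 points, and names no 0–100 scale; its own n, SD, α and power speak against 15 points, since 55 per group would then have about 98.5% power and not 80%. Nor does the range of powers above show that the trial is underpowered, because the bases behind it are assumptions.

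A reader might also take 10.2 points as the difference the sponsor used and so as the relevance threshold. That is circular, since 10.2 is derived from the sample size, and it rests on a two-sided test that the article does not state; a one-sided test gives 9.0.

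On drop-out, it is fair to say that one patient per group is trivial when the 10% is itself an estimate. That limits the size of the point but does not remove it: 55, 10% and 60 stand in one paragraph, conflict without any outside assumption, and no fuller document is needed to see it.

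**Conclusion.** The point holds in two parts of unequal kind.

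- **Drop-out:** wrong as written, and small. The planned 60 per group leaves 54 at the stated drop-out, with about 79% power in place of 80%. Full cover would take 62 per group.
- **Target difference:** not reproducible as stated. The figure of 55 is not shown to be wrong, but the 80% power, and the meaning of a relevant difference, hold for one unstated base only: near 68 if two-sided, about 60 if one-sided.

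The figures rest on a two-group comparison of means with SD 19.0 and equal groups. The planned repeated-measures analysis could have a different power, which the printed inputs do not allow one to work out. Neither part invalidates the design or calls for more patients. Both should be corrected, because the paragraph supplies the yardstick for the primary result.

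**What to change.** Keep 120 patients and revise the Sample Size paragraph.

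1. Restate the allowance in one of two ways: 60 per group covers 8.3% drop-out; or 10% drop-out leaves 54 per group and about 79% power.
2. Have the sponsor state, from its own calculation, the absolute difference in points, the WOMAC score and its scale, the reference mean to which the 15% was applied, and whether the test is one- or two-sided.
3. It may be noted that 55 per group with SD 19 detects about 10.2 points with 80% power at two-sided 5%. Label this as a detectable difference. Use it as the threshold of clinical relevance only if the sponsor confirms that it was the intended difference.

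The cost is restated figures in one paragraph. Enrolment and analysis do not change.

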### Statistical analysis

Descriptive statistics (means and standard deviations) will be used to describe the patient characteristics and outcome variables at the 5 measurement points.

A GLM repeated measures analysis will be used to determine whether there is a difference on the primary and secondary outcome variables between the two groups over time. A p-value of < 0.05 is considered significant.

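### The repeated-measures GLM names no covariate and appears to take the preoperative score as a fifth outcome level; if so, it stays unbiased but is less efficient than adjusting for that score

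*Protocol article*

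**What the plan says.** The Measurements section sets the schedule: "Measurements will take place preoperatively and 6 weeks, 3 months, 6 months and 1 year postoperatively". That is one visit before surgery and four after.

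The Statistical analysis section has two relevant sentences. The first promises means and standard deviations to "describe the patient characteristics and outcome variables at the 5 measurement points", so it counts the preoperative score among the outcome values. The second gives the model: "A GLM repeated measures analysis will be used to determine whether there is a difference on the primary and secondary outcome variables". It sets the comparison as one made "between the two groups over time". It names no covariate, does not list the levels of the time factor, and does not say whether the group main effect or the group-by-time interaction is the deciding test.

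The Sample Size section supplies the scale for the check: "With a standard deviation of 19.0 points, α = 0.05 and power of 80%, 55 patients are needed in each group". It then allows for losses: "With an estimated drop-out of 10% in total 120 patients are needed, 60 patients in each group".

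**The concern.** Before surgery the randomised arms can differ only by chance, so the preoperative score holds no information about the prosthesis design. It does hold information about each patient's later score. A covariate uses that information; a fifth outcome level uses it badly, in a way that depends on the term tested.

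- **Group main effect.** The preoperative visit has an expected difference of zero and takes one fifth of the weight, so the estimated effect shrinks.
- **Group-by-time.** The effect is not diluted, but each contrast of a postoperative visit with baseline is an unadjusted change score that carries the noise of the baseline measurement. The overall test also spreads over 4 degrees of freedom.

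What is at stake is precision on the WOMAC, SF-36 and KSS from data the trial already collects.

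**Working it through.** **Inputs from the protocol article.** SD 19.0, 55 evaluable per group, 60 randomised per group, 10% drop-out, five visits with one preoperative. Analysed per arm: 60 × 0.9 = 54.

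**Assumptions, not in the article.** Two-sided alpha; SD 19 at every visit; a constant postoperative difference; pre-post correlation p from 0.3 to 0.5; post-post correlation q from 0.5 to 0.7.

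**The plan's own figure.** The base of the 15% difference is not given, so 55 per group cannot be confirmed from the stated inputs. The difference that 55 per group implies is 19 × (1.960 + 0.842) × √(2/55) = 10.15 points. I use it only as a scale; the ratios below do not depend on it.

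**Step 1: dilution.** The five-level group effect averages one zero with four postoperative differences: (0 + 4 × 10.15)/5 = 0.8 × 10.15 = 8.12 points.

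**Step 2: variances, in units of 19².**

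- Mean of five visits: V5 = (5 + 8p + 12q)/25
- Mean of four postoperative visits, unadjusted: V4 = (1 + 3q)/4
- The same mean, adjusted for the preoperative score: Va = V4 − p²
- The same mean minus the preoperative score: Vc = V4 + 1 − 2p

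The standard error of a group difference is 19 × √(2/54) × √V = 3.66 × √V. The information ratio of the adjusted mean is V5/(0.64 × Va) against the five-level effect (0.64 = 0.8²), V4/Va against the unadjusted four-visit mean, and Vc/Va against change in the postoperative mean.

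| p | q | V5 | V4 | Va | SE five-level | SE adjusted | Ratio v five-level | Ratio v four-visit | Ratio v change |
|---|---|---|---|---|---|---|---|---|---|
| 0.3 | 0.5 | 0.536 | 0.625 | 0.535 | 2.68 | 2.67 | 1.57 | 1.17 | 1.92 |
| 0.3 | 0.6 | 0.584 | 0.700 | 0.610 | 2.79 | 2.86 | 1.50 | 1.15 | 1.80 |
| 0.3 | 0.7 | 0.632 | 0.775 | 0.685 | 2.91 | 3.03 | 1.44 | 1.13 | 1.72 |
| 0.5 | 0.5 | 0.600 | 0.625 | 0.375 | 2.83 | 2.24 | 2.50 | 1.67 | 1.67 |
| 0.5 | 0.6 | 0.648 | 0.700 | 0.450 | 2.94 | 2.45 | 2.25 | 1.56 | 1.56 |
| 0.5 | 0.7 | 0.696 | 0.775 | 0.525 | 3.05 | 2.65 | 2.07 | 1.48 | 1.48 |

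At p = 0.3 the adjusted SE is about equal to or slightly above the five-level SE. The gain there comes from undoing the 4/5 shrinkage, not from a smaller SE.

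**Step 3: one postoperative visit.** Change score: variance 2(1 − p). Adjusted: 1 − p². Ratio 2/(1 + p): 1.54 at p = 0.3 and 1.33 at p = 0.5. The SEs are 4.33 against 3.49 and 3.66 against 3.17 points. The gap, 2(1 − p) − (1 − p²) = (1 − p)², is never negative.

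**Step 4: power.** With 55 per group, a constant 10.15-point difference and one common correlation ρ for all pairs of visits:

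| ρ | Five-level main effect | Group-by-time, 4 df | Adjusted postoperative mean |
|---|---|---|---|
| 0.3 | 0.92 | 0.64 | 0.995 |
| 0.5 | 0.83 | 0.80 | 0.996 |
| 0.7 | 0.73 | 0.96 | 0.999 |

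**The case against.** **The five-level entry is not stated.** The count of five stands in the descriptive sentence, and the model sentence lists no levels. That sentence is also condensed: it covers all secondary outcomes, and surgical time and blood loss, recorded alongside them, cannot be repeated over visits. An analysis plan that is not shown may settle the matter. All this stands, and the point is therefore conditional. It does not remove the point, because the article does fix a model family and a comparison over time without a covariate. Even if only the four postoperative visits are modelled, adding the covariate gains a factor of 1.13 to 1.67.

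**A reader might infer that the planned analysis is biased or invalid.** It is not. Under randomisation both five-level tests are unbiased, and comparing profiles from the preoperative state is conventional and fits an interest in speed of recovery. A chance preoperative imbalance enters the main effect with weight 1/5 only.

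**A reader might infer that the planned 80% power is lost.** The article does not support that. With a constant effect and 55 per group, the five-level main effect keeps 0.83 or more up to ρ = 0.5, and the interaction reaches 0.80 or more from ρ = 0.5 upwards.

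**A reader might describe the whole interaction test as a change-score analysis.** That fits single baseline-to-visit contrasts, not the 4-df test.

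**The size depends on the shape of the effect.** This also stands. For a difference that starts at 10.15 points at 6 weeks and fades to zero at 1 year (factors 1, 0.66, 0.33, 0), the five-level interaction has power 0.61 to 0.95 over ρ 0.3 to 0.7, against 0.61 to 0.74 for the adjusted postoperative mean. Those two tests ask different questions. Like for like, visit by visit, the adjusted contrast still has the smaller variance (step 3), so a changing effect calls for adjusted visit-specific and group-by-visit results rather than a return to the five-level model.

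**Conclusion.** The point holds as a conditional one about efficiency. As written, the model appears to take the preoperative score as a fifth outcome level. If it does, the group main effect retains 4/5 of a constant postoperative difference, and the interaction is a 4-df test built on unadjusted baseline-to-visit contrasts.

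Under the assumptions listed, the baseline-adjusted postoperative mean carries about 1.4 to 2.5 times the information of the five-level group effect, about 1.5 to 1.9 times that of change in the postoperative mean, and about 1.1 to 1.7 times that of an unadjusted four-visit analysis. A single-visit change score has 33% to 54% more variance than the adjusted comparison. The correlations are assumed, so the sizes are indicative, but the gain has the same direction on each of these readings. The change is worth making; the trial is not invalid without it.

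**What to change.** In the Statistical analysis section, state that the 6-week, 3-month, 6-month and 1-year scores are the repeated outcomes and that the preoperative value of the same measure is a covariate, with a covariate-by-visit term. Apply this to the WOMAC, SF-36 and KSS. Also show the preoperative values in the descriptive table, but do not use them as a level of the time factor. Speed of recovery is still addressed, through group-by-visit over the four postoperative visits.

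The cost is one or two sentences, with no extra patients, visits or data. If an analysis plan already specifies this, the change only brings the article into line with it.

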### Study population

The study will be conducted at the Department of Orthopaedic Surgery of the Martini Hospital, which is a large teaching hospital in the city of Groningen, the Netherlands. Patients who are admitted for primary unilateral TKA due to primary osteoarthrosis are included when the following inclusion criteria are met: non-fixed fixed varus or valgus deformity less than 10 degrees, age between 55 and 85 years, body mass index less than 35 kg/m^2 ^and ASA score (American Society of Anaesthesiologists) I or II.

Patients with secondary osteoarthritis of the knee, rheumatic disease, a flexion less than 90 degrees, a flexion contracture over 10 degrees, peripheral neuropathy or a history of a cerebral vascular accident are excluded. Participation in the study is voluntary and informed consent is required. The inclusion period is planned from January 2008 to January 2010.

If perioperatively an insufficient posterior cruciate ligament is found, the patient will receive a posterior stabilized total knee prosthesis. Analyses will be done according to the intention-to-treat principle, with a sub-analysis excluding these conversions. As the incidence of an insufficient posterior cruciate ligament is higher in patients with secondary osteoarthritis of the knee, rheumatic diseases and a fixed varus or valgus deformity of over 10 degrees, these are exclusion criteria of our study.

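### As ordinarily run, the named GLM repeated measures analysis drops any patient with one missed visit; a mixed model would keep those scores at almost no cost

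*Protocol article*

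**What the plan says.** Four places in the protocol article bear on this point.

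- **Statistical analysis** fixes one method for all outcomes, a GLM repeated measures analysis, to look for a "difference on the primary and secondary outcome variables between the two groups over time".
- **Measurements** sets five time points: "Measurements will take place preoperatively and 6 weeks, 3 months, 6 months and 1 year postoperatively".
- **Study population** says "Analyses will be done according to the intention-to-treat principle, with a sub-analysis excluding these conversions". The sentence follows directly on the rule for patients whose posterior cruciate ligament proves insufficient at surgery.
- **Sample Size** allows for permanent losses only: "With an estimated drop-out of 10% in total 120 patients are needed, 60 patients in each group". This starts from 55 evaluable patients per arm.

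The article does not mention complete cases, deletion of incomplete patients, imputation or an expected rate of missed visits.

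**The concern.** Classical GLM repeated measures treats each patient as one row with a value at every time point. As usually implemented, it discards the whole row if one value is missing. A patient seen before surgery, at 6 weeks, at 3 months and at 6 months, but not at 1 year, would then contribute nothing.

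Three things are at stake:

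1. **Bias.** The complete-case result is in general safe only if scores are missing completely at random. If patients with slow or complicated recovery miss more visits, they are the ones removed, and the comparison can be distorted.
2. **Lost information on recovery.** The Abstract makes speed of recovery part of the objective, so early scores matter even when a later one is absent.
3. **Sample size.** The allowance covers drop-out. Under this method an occasional missed questionnaire costs as much as a drop-out, and nothing is set aside for it.

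**Working it through.** **Inputs from the article.** There are 60 patients per arm, 55 evaluable per arm, 10% drop-out and five measurement points (one preoperative, four postoperative). The standard deviation is 19.0, α is 0.05 and power is 80%.

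**Assumption.** The article gives no missed-visit rate, so a range is used: each visit is missed independently with probability m.

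**Step 1: the plan's own figure.** 110 / 0.9 = 122.2, so 123 patients in total, against the stated 120. The two agree within rounding of about 3%. In the other direction, 60 × 0.9 = 54 per arm, one below 55, so the allowance has no reserve.

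**Step 2: complete cases.** The share with all k visits is (1 − m)^k, and the number left per arm is 60 × (1 − m)^k.

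| m per visit | k = 5: share lost | k = 5: left of 60 | k = 4: share lost | k = 4: left of 60 |
|---|---|---|---|---|
| 1% | 4.9% | 57.1 | 3.9% | 57.6 |
| 2% | 9.6% | 54.2 | 7.8% | 55.3 |
| 3% | 14.1% | 51.5 | 11.5% | 53.1 |
| 5% | 22.6% | 46.4 | 18.5% | 48.9 |

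The k = 4 columns apply if the preoperative score is never missed, which is plausible in patients scheduled for surgery.

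**Step 3: break-even.** The loss equals 10% when (1 − m)^k = 0.9, that is m = 1 − 0.9^(1/k).

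- Five visits: m = 2.1%.
- Four visits: m = 2.6%.

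**Step 4: drop-out and missed visits together.** If 10% leave for good and the others miss visits at rate m, the share left is 0.9 × (1 − m)^5.

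- m = 0: 0.900, or 54 per arm; the loss is exactly the 10% planned.
- m = 1%: 0.9 × 0.951 = 0.856, or 51.4 per arm.
- m = 2%: 0.9 × 0.904 = 0.814, or 48.8 per arm, a loss of 18.6%.

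**Step 5: what a power figure would mean.** The article gives the target difference as 15% and does not convert it to points. Assuming a two-sided test, 55 per arm implies 19 × (1.960 + 0.842) × √(2/55) = 10.15 points, which is 15% of a mean near 68. A two-sample t-test at one time point with that difference has 79.3% power at 55 per arm and 71.7% at 46. These figures are for a single-visit comparison, not for the repeated measures test that the article plans.

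**The case against.** The strongest reply is that this is a condensed article. Handling of missing data is commonly left to the full protocol or the analysis plan, neither of which is shown, and imputation before a GLM would fit the wording and avoid the deletion. That stands as far as the article's silence goes: silence is no defect here. What can be criticised is the named method, because an analysis that follows the section as written inherits its default.

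A reader might also infer four stronger claims, which the article does not support.

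- **That the method contradicts intention-to-treat.** The sentence "Analyses will be done according to the intention-to-treat principle" is tied to conversions, where it means analysis in the allocated arm. GLM repeated measures does not violate that, and nowhere does the article say that incomplete patients are excluded. The broader sense of keeping all randomised patients is not delivered by default, which is a tension and not a contradiction.
- **That the loss will exceed 10%.** With no missed-visit rate this is only conditional. At 2% per visit or less, or with a 10% permanent drop-out and no other missed visits, the loss stays within the allowance. Missed visits that cluster in the same patients would also cost fewer complete cases at the same rate.
- **That power falls to 72%.** That figure belongs to a single-visit t-test at a back-calculated difference. As an illustration, take a common correlation of 0.5 and a constant 10.15-point difference. With 46 per arm, a between-group test averaged over the four postoperative visits has about 89% power; with baseline as a fifth level, about 75%. The article states neither the correlation nor which term is tested.
- **That non-sphericity invalidates the test.** Standard corrections and multivariate tests exist, and the article does not commit to an uncorrected univariate test. This is a minor matter.

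**Conclusion.** The point holds as a weakness in the choice of method, stated conditionally. Run in the ordinary way over five visits, the named analysis removes every patient with a gap, and so discards observed scores and relies on a stronger missing-data assumption than it needs to. The number lost depends on a rate that the article does not give: about 3 to 14 of 60 patients per arm for 1% to 5% missed independently at each of five visits. The 10% allowance is passed only above about 2.1% per visit (2.6% if only postoperative visits can be missed), or when missed visits are added to a full 10% drop-out. Bias is possible, but its size cannot be derived from the article. No loss of power for the planned test can be stated either. Because a better method is available at almost no cost, the change is worth making even if few visits are missed.

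**What to change.** In the Statistical analysis section, replace the GLM repeated measures analysis with a likelihood-based linear mixed model for repeated measures. It should have visit as a category, treatment, treatment-by-visit interaction and an unstructured covariance over visits. It should use all available scores from all randomised patients as allocated, with no deletion of patients for a missed visit. The planned sub-analysis without conversions can use the same model.

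This analysis is valid under missing at random, a weaker condition than complete-case analysis generally needs, and it does not require sphericity. It does not protect against missingness that depends on the unseen scores themselves.

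The cost is a change of wording and slightly more modelling work. It needs no extra patients, visits or data, and standard packages can fit the model.

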## Abstract

**Background:**

Prosthetic design for the use in primary total knee arthroplasty has evolved into designs that preserve the posterior cruciate ligament (PCL) and those in which the ligament is routinely sacrificed (posterior stabilized). In patients with a functional PCL the decision which design is chosen depends largely on the favour and training of the surgeon.

The objective of this study is to determine whether the patient's perceived outcome and speed of recovery differs between a posterior cruciate retaining total knee arthroplasty and a posterior stabilized total knee arthroplasty.

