The primary objective of this randomized controlled trial is to examine whether there is a difference in patient's perceived outcome as determined with The Western Ontario and McMaster Universities Osteoarthritis Index (WOMAC) between a patient group receiving a posterior cruciate retaining total knee arthroplasty compared to a group receiving a posterior stabilized total knee arthroplasty.

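### The stated 80% power is for a single two-group difference and is not tied to the planned repeated-measures test, which alone would not separate final outcome from speed of recovery

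*Protocol article*

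**What the plan says.** The Sample Size section of the protocol article rests on one contrast: "A difference between the two groups of 15% is considered clinically relevant". It continues: "With a standard deviation of 19.0 points, α = 0.05 and power of 80%, 55 patients are needed in each group". It names no visit, no number of repeated measurements and no within-patient correlation.

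The Statistical analysis section plans a GLM repeated-measures analysis of a difference "between the two groups over time. A p-value of < 0.05 is considered significant". The Measurements section lists one pre-operative and four post-operative assessments (6 weeks, 3 months, 6 months, 1 year). The text does not say whether the group term, the group-by-time term or a contrast at one visit decides, nor whether the pre-operative value is a level of the time factor.

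The abstract sets a two-part aim: "whether the patient's perceived outcome and speed of recovery differs between a posterior cruciate retaining total knee arthroplasty" and a posterior stabilized one. The abstract's discussion and the main Discussion repeat the interest in speed of recovery. The Background gives a narrower primary aim, with no time point: "The primary objective of this randomized controlled trial is to examine whether there is a difference in patient's perceived outcome" on the WOMAC. No measure or contrast is given for speed of recovery.

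**The concern.** A sample-size statement is useful only if its power belongs to the test that will be run. Here the calculation is for a two-sample comparison of means, whereas the analysis is an omnibus comparison over several visits. A repeated-measures GLM gives both a group F-test and a group-by-time F-test. The power of each depends on the pattern of the difference over time and on the correlation between visits, and the sample-size section mentions neither.

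Interpretation is also at stake. The study wants to know about outcome and about speed of recovery. A difference that fades after 6 weeks and one that is present at 1 year answer different questions, yet both could be reported as the same significant difference over time. With no deciding term fixed in this document, the choice could also be made after the results are seen.

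**Working it through.** **Inputs from the protocol (Sample Size):** SD 19.0, α = 0.05, power 80%, n = 55 per arm. Two-sided testing is assumed because sidedness is not stated.

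**Assumed, not in the protocol:** compound symmetry with within-patient correlation ρ = 0.3, 0.5 or 0.7; the patterns of difference over time; and, in step 2, baseline as one of five levels of time.

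**1. The plan's own figure.** For two means, n = 2·SD²·(1.960 + 0.842)²/d².
- Reading 15% as 15 points: 2 × 361 × 7.85/225 = 25.2, so 26 per arm, not 55.
- Solving for d at n = 55: d = 19.0 × √(2/55) × 2.802 = 10.15 points. This is 15% of about 68 points (10.15/0.15 = 67.7), a base the protocol does not state.

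The figure of 55 thus fits a single two-group contrast of about 10.2 points. I use d = 10.15 below.

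**2. Power of the two F-tests the GLM produces, five levels of time.**

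Group-by-time non-centrality: λ = (n/2)·Σ(δₜ − mean δ)²/[SD²(1 − ρ)], on 4 and 432 df.
- Equal difference at all four post-operative visits (0,d,d,d,d): Σ = 0.64d² + 4 × 0.04d² = 0.8d².
- 6 weeks only (0,d,0,0,0): Σ = 0.8d².
- 1 year only (0,0,0,0,d): Σ = 0.8d².

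At ρ = 0.5, λ = 27.5 × 0.8 × 10.15²/(361 × 0.5) = 12.56 for all three.

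Group non-centrality: λ = (n/2)·(mean δ)²/[SD²(1 + 4ρ)/5], on 1 and 108 df. For 1 year only at ρ = 0.5: 27.5 × 2.03²/(361 × 0.6) = 0.52.

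| Pattern of difference | Group-by-time power, ρ = 0.3/0.5/0.7 | Group power, ρ = 0.3/0.5/0.7 |
|---|---|---|
| 1 year only | 66/82/97% | 13/11/10% |
| 6 weeks only | 66/82/97% | 13/11/10% |
| All post-operative visits | 66/82/97% | 92/82/72% |
| Linear growth to 1 year | 54/70/92% | 55/43/36% |

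**3. Same check with only the four post-operative visits in the time factor.** The group-by-time test has 67/83/97% power for 6 weeks only and for 1 year only. For a constant difference its non-centrality is 0, so its rejection rate is 5%. The group test has 17/14/12% power for either single-visit pattern and 98/94/88% for the constant one. Which term decides then matters even more.

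**4. Type I error if either F-test may count.** 1 − 0.95² = 9.75%, treating the two tests as independent. A null simulation at ρ = 0.5 (20,000 runs) gave 9.6%.

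**5. A single named contrast, for comparison.** For the 1-year difference at 55 per arm and 10.15 points, an unadjusted t-test has 79% power. With baseline as a covariate the residual variance is SD²(1 − ρ²). At ρ = 0.5, λ = 27.5 × 10.15²/(361 × 0.75) = 10.5. Power is 83/89/97% at ρ = 0.3/0.5/0.7.

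**The case against.** The strongest reply is that the deciding term, the time point, the handling of baseline and multiplicity are commonly left to a statistical analysis plan, which is not shown, and that this is a condensed article. The model family is valid for repeated measures, and nothing in the analysis section is false. That stands, so the absence of such detail is not itself the point. What remains is that two elements the article does state, the power and the test, do not refer to the same quantity.

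Four stronger readings are tempting and are not supported.
- **The trial is underpowered.** At ρ = 0.7 the group-by-time test has 97% power in three of the patterns above. If 15% means 15 points, it has 96% power for a single-visit difference even at ρ = 0.3.
- **The type I error is doubled.** The 9.75% applies only if a significant result on either term is allowed to count. The text neither says so nor excludes it, and it can be read as a single test.
- **The analysis can never tell early from late.** Equal power across patterns needs compound symmetry and baseline as a level. Under an assumed AR(1) correlation of 0.7, a multivariate group-by-time test has 98% power for 6 weeks only and 84% for 1 year only. The two F-tests read together carry some information on shape, and means and SDs are to be described at all five points.
- **The abstract contradicts the primary objective.** The two are a wider and a narrower aim.

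**Conclusion.** The point holds in a limited form. The 80% belongs to a single two-group contrast and is not tied to the planned repeated-measures test. For 10.15 points at 55 per arm, the power of that analysis runs from about 10% to 97%, depending on the term, the pattern of difference and the correlation. These figures rest on a back-solved difference, assumed correlations and compound symmetry. They show that the stated power is unanchored, not that it is too low.

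A significant omnibus F-test alone would not show whether final outcome or speed of recovery differs, and speed of recovery is a declared interest of the study. That conclusion does not depend on whether baseline is in the time factor: in steps 2 and 3 the group-by-time test has the same power for a purely early and a purely late difference, under compound symmetry. The change is worth making, but the point does not invalidate the design.

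**What to change.** Pre-specify one primary contrast: a between-arm difference in WOMAC from the repeated-measures model with baseline as a covariate, tested two-sided at 5%. The 1-year difference is one example. Another single contrast, such as the mean of the post-operative visits, would serve if the sponsor prefers it, given the study's interest in more than the final result.

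Tie the sample-size statement to that contrast by naming the visit or summary, the difference in points and the matching SD. For the 1-year contrast, 55 per arm already fits a difference of about 10.2 points. If a mean over visits is chosen, the SD must be that of the mean.

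Name speed of recovery as a separate secondary contrast, reported with a 95% CI: the early between-arm difference (mean of 6 weeks and 3 months) minus the 1-year difference.

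The cost is a few sentences in the objective, sample-size and analysis sections, with no added patients or visits. The downside is that the other visits and the omnibus F-tests become secondary.
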